## Background

Cognitive impairment (CI) including dementia and delirium are common amongst older people admitted to acute hospitals [1–3]. Patients with these conditions have a significantly increased risk of serious adverse outcomes when hospitalized, compared with same-aged patients without CI. For instance, dementia is a key risk factor for the development of delirium (patients with dementia have a five to six-fold increased risk of developing delirium than other patients of the same age), which is associated with high morbidity and mortality in older people [4]. Other adverse outcomes associated with both dementia and delirium include cognitive and functional decline, medical and surgical complications, significantly increased risk of falls and longer hospital stays and greatly increased hospital costs [2, 4, 5].

Despite their high prevalence and associated adverse outcomes, dementia and delirium are frequently not recognized or recorded in acute hospitals with delirium being missed in as many as 75% of cases [6–9]. Consequently, appropriate prevention and management strategies [6, 8], are not implemented, which effectively prevent delirium in many at-risk patients [4, 10]. An important reason for the under-recognition of delirium is that nurses working in acute hospitals do not receive adequate or appropriate education in identifying and caring for patients with CI [1, 11]. Accordingly, addressing this issue and ensuring that staff are knowledgeable and adequately skilled to identify and care for these patients has been identified as a key strategy for improving these patients’ care [1, 11–15].

Currently, however, the most effective way of educating staff and initiating practice change for older patients with CI in the hospital environment is unclear, as limited research has been undertaken in this area. Of the studies that have been reported, results generally indicate that, while education can improve knowledge of dementia [13, 16], and delirium [17], education in isolation has little effect on clinical practice [18]. By comparison, the use of knowledge translation principles has been shown to be more effective in producing practice change and preventing delirium [10, 18, 19], and are recommended [20, 21].

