Increased proportion of older patients who are routinely assessed for CI at admission to the hospital.	Room & Chart Audit/Observation tool These data will be collected on multiple occasions throughout the project – (1) Pre- intervention, (2) Following the CogChamps training, (3) Following the implementation of ward specific Action Plans, and (4) Three months following withdrawal of the research team.	The room & chart audit/observation tool included an item regarding cognitive assessment – ‘There is documentation that the patient’s cognitive function was assessed using a standardized assessment tool within 24 h of admission to the ward’. This item was adapted from a similar item developed by Schnitker and colleagues for use in the hospital Emergency Department [38].
Increased implementation of best practice guideline for delirium prevention, management and treatment.	Audits of patient rooms and charts. These data will be collected on the same four occasions as the previous item. Direct observations of Nurse: patient interactions.	The room & chart audit/observation tool includes questions relating to cognitive assessment, pain assessment and management (e.g., Was a pain assessment undertaken? Had analgesia been administered within the last 24 h?), and antipsychotic/benzodiazepine use (Was the patient prescribed or administered any PRN antipsychotic/benzodiazepine medication within the past 24 h?). Items requiring direct observation include aspects of the environment (e.g., Was there a clock set to the correct time, that the patient could see from his/her bed?); nutrition (Was adequate assistance provided to the patient if the patient had difficulty eating or drinking); restraint use (Was the patient restrained?); use of indwelling catheters (IDC; Did the patient have an IDC in situ?), communication (If the patient exhibited confusion/dis-orientation, did the nurse say anything to re-orient the patient?), and patient activity (What was the patient doing when you entered the room?).
Older patients with CI will have fewer adverse outcomes.	Data regarding adverse outcomes from the hospital’s administrative database will be extracted at each data collection point and compared across data collection points and between the IH and CH.	Data regarding falls and antipsychotic use will be obtained from the hospital’s database.

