#### Procedure for collecting evaluative data

The audits/observations will be completed by two Research Nurses who will be seconded from other hospital wards at the IH (and hence will be familiar with the hospital and its processes), to work on the project. They will be trained to use the tool by CT, and practice cases will be completed (not for inclusion in the final dataset) until an inter-rater agreement of 90% is achieved [32]. The same two nurses will collect the data on each occasion.

The audits/observations will be undertaken for one full day in each of the six intervention and two control wards on each of the five data collection occasions (i.e., a total of 40 days). The data collection is scheduled to occur over the second half of the month on each occasion, and the specific ward to be audited for the day will be randomly selected, using SPSS’s randomization function. One week prior to data collection, each ward’s Nurse Unit Manager will be informed via email, of the day their ward will be scheduled for data collection.

On each audit morning, the Research Manager (CT) will identify all patients with a documented diagnosis of dementia or delirium, or report of confusion, memory problems or other CI in the patient’s chart, or reported verbally by the Charge Nurse. While it is acknowledged that a formal assessment process would be required to be completely confident that all patients with CI are included, this method described is considered adequate for this study. Moreover, the inclusion of patients identified by a nurse with first-hand knowledge of the patients as likely having CI, will overcome some of the under-reporting of dementia in hospital records [8].

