A maximum of eight patients will be selected per day, and allocated equally to each Research Nurse. Where more than 8 patients are identified on a particular day, eight patients will be selected using a commercially available random number generator (42 Random Number) APP downloaded onto an Android smart phone. Each patient will be audited/observed on four separate occasions throughout the day: early morning (7 am–9.30 am), late morning (9.30 am–12.00 noon), early afternoon (12.00 noon–1.30 pm) and mid-afternoon (1:30 pm–3:00 pm). The Research Nurse will be required to remain in the patient’s room for at least 15 min per observation and at least one meal-time will be observed. Research Nurses will be instructed to conduct the observations as unobtrusively as possible, and to be polite if patients speak to them but not to encourage conversation.

As no personally identifying information will be recorded for either nurse or patient, obtaining individual informed consent from each participant is not required by the relevant Ethics Committees. Hence, the participation rate is expected to be very high and patients will be excluded only if the patient is likely to be absent from their room for much of the observation period (e.g., a procedure is scheduled).

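### The admission-assessment item looks back to each patient's first 24 h on the ward but is scored on whoever is there on audit day, so the post-training audit can mix in earlier practice, to an extent the article does not allow one to fix

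*Protocol article*

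**What the plan says.** In Table 2 (Expected outcomes and project evaluation), the outcome is: "Increased proportion of older patients who are routinely assessed for CI at admission to the hospital". The audit item behind it asks whether there is documentation that "cognitive function was assessed using a standardized assessment tool within 24 h of admission to the ward". The second and third audit occasions are placed as "2) Following the CogChamps training, (3) Following the implementation of ward specific Action Plans", after a pre-intervention audit and before a follow-up three months after the research team withdraws. I call these collections 1 to 4, in Table 2's order.

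Under Procedure for collecting evaluative data, the Research Manager "will identify all patients with a documented diagnosis of dementia or delirium, or report of confusion, memory problems or other CI" on each audit morning, from the chart or from the Charge Nurse's report. "A maximum of eight patients will be selected per day", and "patients will be excluded only if the patient is likely to be absent from their room for much of the observation period". No condition on admission date is stated. The Evaluation tool section says that most items can be answered Yes, No or Not applicable.

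On timing, Table 1 puts the two workshops about two months apart. The Confusion Assessment Method (CAM) is taught in Workshop 1, and competency is consolidated in the month after it. Workshop 2 covers leadership skills and Action Plans. Collection 2 follows the workshops by an unstated interval. Action Plans then run for 4–6 months before collection 3.

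**The concern.** The item is dated to arrival on the ward, whereas the sample is dated to the audit day. A patient already on the ward when training finished carries the practice of an earlier phase into an audit labelled post-training. If training truly raises assessment, such patients pull the collection 2 rate back towards baseline. The change from collection 1 to 2 is then understated, and the missing part appears between collections 2 and 3. The control hospital has no training step, so the contrast between hospitals at collection 2 shrinks as well.

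This matters because the Discussion relies on the successive time points to show which parts of the implementation produced any change. Effect assigned to the wrong interval credits Action Plan implementation with some of what training achieved.

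There is a smaller problem at the other end. A patient on the ward for less than 24 h is scored before the assessment window has closed, unless Not applicable is used. The items that ask about the past 24 h (analgesia, as-needed drugs) then also reach back before arrival.

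**Working it through.** **The plan's own figure.** The article plans one audit day in each of the "six intervention and two control wards on each of the five data collection occasions (i.e., a total of 40 days"): (6 + 2) × 5 = 40, which reproduces. (Table 2 lists four occasions, which would give 32 days. That needs reconciling but does not affect this point.) With at most 8 patients per ward-day, an occasion has at most 6 × 8 = 48 intervention and 2 × 8 = 16 control patients.

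**Inputs not in the article, assumed here.** Exponential ward stays with mean L of 7 to 20 days; collection 2 at 7 or 28 days after Workshop 2; two months taken as 60 days and the competency month as 30; a true rise from 20% to 50%, for illustration only.

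**Share of earlier admissions.** With exponential stays, time already spent on the ward by a patient present on a random day is also exponential with mean L. The share admitted more than d days before the audit is f = exp(−d/L). The observed rate is 0.20f + 0.50(1 − f) = 0.50 − 0.30f.

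| Audit after Workshop 2 | Step counted from | d (days) | f at L = 7 | f at L = 20 | A true 50% reads as |
|---|---|---|---|---|---|
| 7 days | Workshop 1 | 60 + 7 = 67 | 0.01% | 3.5% | 49–50% |
| 7 days | End of competency month | 67 − 30 = 37 | 0.5% | 16% | 45–50% |
| 7 days | Workshop 2 | 7 | 37% | 70% | 29–39% |
| 28 days | Workshop 2 | 28 | 2% | 25% | 43–49% |

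**Cross-check.** Audits are spread over the second half of a month. Averaging over a 15-day window that starts g days after the step gives f = (L/15)[exp(−g/L) − exp(−(g + 15)/L)]. For g = 7 this is 19% at L = 8 and 40% at L = 15. For g = 60 it is 0% and 1%.

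**Effect on precision.** Comparing 48 with 48 patients at two-sided 5% and ignoring ward clustering, power for 20% v 50% is 88% with f = 0, 81% with f = 10%, 67% with f = 25% and 49% with f = 40%.

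**Later audits.** Patients admitted before implementation began 4 months earlier (about 120 days) are at most exp(−120/20) = 0.2% at collection 3. Patients admitted before withdrawal (about 90 days) are at most exp(−90/20) = 1.1% at follow-up.

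**Open window.** The share on the ward for under 24 h is 1 − exp(−1/L): 13% at L = 7 and 5% at L = 20.

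**The case against.** The strongest reply concerns the starting date. Assessment with the CAM is taught in Workshop 1, about two months before Workshop 2, so few patients on the ward at collection 2 could pre-date it. This stands, and it largely removes the problem for any effect that begins with Workshop 1. It does not remove it altogether: competency is built over the following month with repeat observation if needed, change-management skills come only in Workshop 2, and no stated gap rules out an early audit.

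A reader might infer that the post-training result is certainly and heavily biased towards no change. The article does not support that. It gives no length of stay, audit gap, baseline rate or expected effect, and the Background says only that these patients have a "significantly increased risk of falls and longer hospital stays". Dilution also requires a true rise by collection 2. Six nurses per ward are trained, and any spread to colleagues comes largely with the Action Plans, so that rise may be small.

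A reader might also infer that over-sampling of long stayers, or the patients under 24 h on the ward, distorts the change over time. Both arise under the same sampling rule at every occasion and both hospitals. They affect the level of the rate and whom it describes more than the contrast.

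Finally, the audit form is not shown, and Not applicable could be used for open windows or earlier admissions. That is possible, but no such rule is stated, and the exclusion rule that is stated is a closed one.

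**Conclusion.** The mismatch follows from the stated rules: an item dated to admission, a sample dated to the audit day, and one exclusion unrelated to admission date. Given a true benefit of training, its direction at collection 2 is towards a smaller change from baseline and a larger change in the next interval.

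Its size is conditional. It is negligible for effects that start at Workshop 1, up to about 16% of patients if practice changed only once competency was consolidated, and large (37–70%) only for effects that begin at Workshop 2 with an audit a week later. These shares rest on assumed exponential stays of mean 7 to 20 days. The comparison of baseline with collection 3 or with follow-up largely survives. What is weakened is the attribution between training and implementation, for this one item.

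**What to change.** Add one non-identifying field to the audit form: hours or days since arrival on this ward. Because no identifying data are kept, it probably cannot be recovered later.

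- Score the admission item only in patients at least 24 h on the ward.
- Report it also in patients who arrived within one fixed look-back window, chosen so that at collection 2 the whole window falls after the training step. State which date counts as the end of that step.
- Apply the same window at every occasion and at both hospitals. Restricting only the post-step audits would compare recent arrivals with an unrestricted baseline and create a new difference in case mix.
- Keep the full audited set alongside.

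The cost is one field and a smaller denominator for this item. The share kept with a window of w days is exp(−1/L) − exp(−w/L). For w = 7 this is 50% at L = 7 and 25% at L = 20, or about 24 and 12 of 48 intervention patients and 8 and 4 of 16 controls. For w = 28 it is 85% and 70%, or about 41 and 34 of 48 and 14 and 11 of 16. A short window may therefore leave too few control patients to be useful, which is a further reason to keep the full set.

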### Expected outcomes and project evaluation

Expected project outcomes include:➢ Increased nurses’ knowledge of CI and self-confidence in nursing patients with CI;➢ Increased number of nurses in the IH who are proficient in assessing and documenting dementia and delirium;➢ Increased number of patients assessed for CI at admission to hospital (IH);➢ Improved outcomes of nursing care practices for older patients with CI (e.g., improved pain management, nutrition & hydration, patient mobilization) [12, 24], and➢ Reduced adverse outcomes for older patient with CI in hospital (i.e., falls, antipsychotic use).

Each of these outcomes is being evaluated as outlined in Table 2.

**Table 2 Tab2:** CogChamps: Expected project outcomes and evaluation methods

Expected outcome	Evaluation Method	Tool/Details
Increased Nurses’ knowledge of dementia and delirium	Delirium knowledge questionnaire administered immediately prior to Workshop 1, and re-administered immediately prior to Workshop 2. CogChamps will also be encouraged to administer this tool to other nurses on their wards prior to, and following any CI education they undertake, if CI education is included in their ward’s Action Plan.	The questionnaire includes 15 True/False items relating to delirium features and risk factors, and five validated vignettes, developed specifically for nurses [34]. Five vignettes will be included in the baseline questionnaire and another five (matched for diagnostic complexity) will be administered at follow-up. True/False items - As a literature search failed to identify any well validated tools for assessing nurse’s delirium knowledge, the 15 items common to the Delirium Knowledge Questionnaire [35] and an assessment tool developed by Wand and colleagues [36] were selected.
Increased Nurses’ self-confidence when nursing patients with delirium or confusion	Single item assessing nurses’ self-confidence administered immediately prior to Workshop 1 and re-administered immediately prior to Workshop 2.	Single item statement answered using a 1–5 scale where 1 = not at all confident and 5 = very confident. The item was a slight adaptation of a previously used item [37].
Increased number of nurses at the IH who are proficient in assessing delirium.	Direct observation of CAM administration and interpretation by an expert. Following Workshop 1.	Proficiency will be established by observing CogChamps administer a CAM to a patient and interpret it.

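### Falls and antipsychotic use are compared in patients with CI, but the intervention may change who is recorded as having CI at the intervention hospital only

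*Protocol article*

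**What the plan says.** All references are to the Protocol article.

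- **Outcome and population.** The section on expected outcomes and project evaluation lists, as a project aim, "Reduced adverse outcomes for older patient with CI in hospital (i.e., falls, antipsychotic use"). The matching row of Table 2 reads "Older patients with CI will have fewer adverse outcomes".
- **Source and comparison.** The same row says "Data regarding falls and antipsychotic use will be obtained from the hospital"'s database, and that the data "will be extracted at each data collection point and compared across data collection points and between the IH and CH".
- **Recognition before the intervention.** The Background says dementia and delirium often go unrecognised or unrecorded in acute hospitals, with up to 75% of delirium cases missed. The procedure for collecting evaluative data also acknowledges that hospital records under-report dementia.
- **What the intervention is meant to change.** The expected outcomes include more IH nurses able to assess and document dementia and delirium, and more IH patients assessed for CI at admission.
- **How CI patients are found.** The only route described is for the audit: a chart entry or a verbal report by the Charge Nurse. No route is given for the database extract.

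**The concern.** The population in which adverse outcomes are measured is defined by a characteristic that the intervention is designed to make more visible. At baseline, the IH patients known to have CI are those whom staff had noticed without the programme. After training, the same label may cover additional patients who would previously have gone unrecorded. If their underlying risk differs from that of patients already recorded, the rate in the labelled group moves even though no individual patient's risk has changed.

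A control hospital normally protects a before-after comparison against influences shared by both sites. This influence is not shared, because the CH receives no programme to raise recording. The shift therefore passes straight into the IH-versus-CH difference in change. A favourable result could be read as fewer falls and less antipsychotic use when only the case mix had altered. Equally, a real improvement could be hidden.

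**Working it through.** **The plan's own figures.** The article gives no event rate, denominator, sample size or target difference for falls or antipsychotic use, so there is no figure of its own to reproduce for this outcome. The nearest count is the audit schedule: "each of the six intervention and two control wards on each of the five data collection occasions (i.e., a total of 40 days"). This checks, as (6 + 2) wards × 5 occasions = 40, but it describes audit days and not the database extract.

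**Set-up.** Suppose nothing truly changes in the events. Let

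- s0 = share of CI patients recorded as such before the intervention;
- s1 = share recorded afterwards;
- k = event rate in newly recorded patients divided by the rate in those already recorded.

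The apparent rate ratio, after versus before, in recorded-CI patients is

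RR = [s0 + (s1 − s0) × k] / s1.

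**Inputs.** s0 = 0.25 is taken from the Background (up to 75% missed). That figure is an upper limit and concerns delirium, not all CI, so s0 = 0.50 is shown too. The values of s1 and k are assumptions; the article gives neither.

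**Results for s0 = 0.25, s1 = 0.60:**

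- k = 0.50: (0.25 + 0.35 × 0.50) / 0.60 = 0.425 / 0.60 = 0.71
- k = 0.75: (0.25 + 0.35 × 0.75) / 0.60 = 0.5125 / 0.60 = 0.85
- k = 1.00: (0.25 + 0.35) / 0.60 = 1.00
- k = 1.25: (0.25 + 0.35 × 1.25) / 0.60 = 0.6875 / 0.60 = 1.15

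**Results for a smaller shift, s0 = 0.50, s1 = 0.75:**

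- k = 0.50: (0.50 + 0.25 × 0.50) / 0.75 = 0.625 / 0.75 = 0.83
- k = 0.75: (0.50 + 0.25 × 0.75) / 0.75 = 0.6875 / 0.75 = 0.92
- k = 1.00: 0.75 / 0.75 = 1.00
- k = 1.25: (0.50 + 0.25 × 1.25) / 0.75 = 0.8125 / 0.75 = 1.08

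**Effect on the between-hospital contrast.** If recording at the CH stays constant, its ratio is 1.00. The IH-versus-CH ratio of ratios then equals the IH ratio, for example 0.71 / 1.00 = 0.71. The control comparison removes none of the shift.

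**Why a wider denominator helps.** The rate in all older patients is their total events divided by their total occupied bed-days. Neither term contains s0 or s1, so a change in recording alone cannot move it. The price is dilution. If a share c of all events occurs in patients with CI, and the true rate ratio in them is θ, the ratio in all older patients is 1 − c(1 − θ), which lies closer to 1 than θ whenever c is below 1.

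**The case against.** **The mechanism is partly inferred.** Nothing in the article says that ward CI assessments feed the administrative codes, or that database codes identify the CI group. This stands as a limit on certainty. It does not remove the problem, because the one identification route described, for the audit, also depends on what staff have written down or noticed. Adding the Charge Nurse's report was meant to offset some under-reporting, but staff awareness is itself a target of the programme.

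**The direction is not known.** A reader might infer that better recording must lower the rate because newly recorded patients are milder. The article does not say they are. At equal risk there is no bias, and at higher risk it reverses. This objection stands in full.

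**Details may sit elsewhere.** A condensed article commonly leaves the extract window, denominator and case definition to a fuller document, and their absence is not the point here. The point rests on what the article does state: population, source, comparison, and an intervention aimed at recognition.

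**Two stronger readings are tempting and unsupported.**

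- *That events are compared only for short periods at the collection points.* Table 2 fixes when data are extracted, not the period each extract covers, which could be the whole interval since the previous one. The half-month timing, "The data collection is scheduled to occur over the second half of the month on each occasion", is given for the audits.
- *That falls will be too few to interpret.* The article gives no fall rate, ward size or window. Assuming 3 to 15 falls per 1,000 patient-days, eight CI patients per ward and a true halving at the IH, power for the IH-versus-CH difference in change is 5–11% with half-month windows and 22–75% with six-month windows. For the IH before-after comparison it is 9–26% and 53% to over 99%. These figures ignore ward clustering, and the census of eight is borrowed from the audit cap ("A maximum of eight patients will be selected per day"). The answer depends on inputs that the article does not supply.

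**Conclusion.** The concern holds as a bias of unknown sign and size. Falls and antipsychotic use are to be compared in a group whose membership can change at the IH, and not at the CH, as a direct result of the intervention working as intended. The planned contrast cannot separate that change from a real effect.

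In the illustrations above, the apparent rate ratio with no true change runs from 0.71 to 1.15 when recording rises from 25% to 60%, and from 0.83 to 1.08 when it rises from 50% to 75%, for relative risks k between 0.50 and 1.25. These ranges rest on assumed recording levels and assumed risks, on stable recording at the CH, and on the inference that the CI group is found through what staff recognise or record. They show what could happen and do not predict the result. The point merits a change before the data are extracted. It does not affect outcomes that are not defined by CI status.

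**What to change.** Amend the adverse-outcomes row of Table 2 as follows.

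1. Extract falls, antipsychotic use and occupied bed-days for **all** older patients on the six IH and two CH wards, using the same age limit and identical fixed windows at both hospitals.
2. Base the IH-versus-CH before-after comparison on rates per 1,000 occupied bed-days in that population.
3. Report the recorded-CI subgroup alongside, stating how CI is identified in the database, and show the proportion of older patients recorded as having CI at each point and hospital. A rise in that proportion at the IH alone would warn the reader that the subgroup rate may reflect case mix.
4. Where the database allows, include earlier pre-intervention periods at both hospitals to show the prior trend. The article describes seven years of CI education and other initiatives at the IH before this project, so a trend is plausible.

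While amending the row, reconcile the number of collection points. The procedure section counts five, whereas for the audits Table 2 says "These data will be collected on the same four occasions as the previous item".

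**Cost.** A wider query on the same source and a little more analysis. The effect in all older patients will be diluted by those without CI, which is why the subgroup should still be shown.
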